### Ensuring complete follow-up

The following measures will help to ensure completion of follow-up: a) study patients will supply their own address, telephone and email information as well as the name, relationship, address, telephone and email information of someone who does not reside with the patient, but is likely to have contact with them should they move or change telephone information, b) patients will receive a copy of the consent form which will outline the purpose of the study, the importance of their individual participation and attendance for follow-up assessments and c) the research coordinator will maintain regular contact with the patients.

### Statistical considerations

#### Primary analysis

The primary analysis involves a comparison of the MEPS outcome measure between the two surgical treatment groups on an intention-to-treat basis at 24 months post-surgery as compared to baseline values. A two-sample independent ANCOVA will be used to assess whether there is a statistically significant difference between groups for the MEPS scores, accounting for the debridement stratification variable and baseline MEPS. Linear regression will be used to estimate treatment size effect, accounting for the stratification variable and baseline MEPS, as well as any possible imbalanced covariates. Primary analyses will be repeated for the debridement and no-debridement patient subgroups. Missing follow-up data will be addressed with multiple imputation techniques.

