**Methods:**

We will conduct a prospective single center, double-blind, randomized sham-controlled parallel arm trial evaluating the efficacy of arthroscopic tennis elbow release in adult patients with symptoms for at least 6 months. Patients will undergo intraoperative randomization after diagnostic arthroscopy of the elbow to receive either ECRB release (through the creation of a lateral portal) or a sham lateral portal and no ECRB release. The primary outcome will be the Mayo Elbow Performance Score (MEPS) at 1 year follow-up. Secondary outcomes will be the abbreviated Disability of the Shoulder and Hand (DASH) score, American Shoulder and Elbow Surgeons elbow (ASES-e) score and grip strength at 3, 6, 12 and 24 months as well as return-to-work time, ability to return to full duty and adverse outcomes.

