### Purpose and hypothesis

The purpose of the study is to determine whether ATER is superior to non-operative management using a sham surgery control group for the management of chronic lateral epicondylitis of the elbow at 24 months postoperative as measured by the Mayo Elbow Performance Score (MEPS). Data will be collected at baseline and at 3, 6, 12 and 24 months following surgery. In addition, we will aim to determine if there is a differential effect of ATER versus sham surgery among the subgroup of patients requiring additional elbow debridement due to coexisting intra-articular pathology. Furthermore, we will compare the effect of ATER and sham surgery on the abbreviated DASH and American Shoulder and Elbow Surgeons Elbow (ASES-e) scores at the different timepoints, as well as assess for any differences in grip strength, return to work time and adverse outcomes between the two groups.

We hypothesize that at 24 months, the improvement in MEPS is greater after ATER than sham surgery. Furthermore, we hypothesize that the DASH, ASES-e will also favor ATER at all postoperative timepoints. In addition, we hypothesize that grip strength will be diminished in the ATER group compared to sham, but that return to work time will favor ATER Table 1.

**Table 1 Tab1:** Data collection timeline

Variable	Baseline^a^Preoperative	T = 2 weeks Postoperative	T = 6 weeks Postoperative	T = 3 months Postoperative	T = 6 months Postoperative	T = 1 year^b^Postoperative	T = 2 years Postoperative
*Patient demographics*							
Age (years)	X						
Sex (M/F)	X						
Duration of symptoms (months)	X						
Arm affected (L/R)	X						
Dominant arm (L/R)	X						
Height (cm)	X						
Weight (kg)	X						
Body-Mass Index (BMI)	X						
Occupation	X						
Smoker (Y/N)	X						
Diabetic (Y/N)	X						
*Outcome measure*							
MEPS^c^	X			X	X	X	X
*Quick*DASH	X			X	X	X	X
ASES-e	X			X	X	X	X
Grip strength (grip dynamometer)	X			X	X	X	X
Return to work (Y/N)				X	X	X	X
Complications		X	X	X	X	X	X

^a^Second clinical visit

^b^Primary endpoint

^c^Primary outcome measure

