### Primary outcome

#### MEPS

All functional assessment forms will be administered electronically to patients by means of a touch-screen device at each follow-up appointment. Our primary outcome measure is elbow pain and function as measured by the MEPS at 24 months post-operative. The MEPS is a commonly used performance index for evaluation of clinical outcomes for a variety of elbow disorders that can be completely patient-administered [28]. It consists of four parts: pain, stability, ulnohumeral motion and the ability to perform five functional tasks. The highest possible score is 100, with scores 90 and above indicating excellent function [29].

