### Control of contamination and co-intervention

There will be a possibility of cross-over after one year postoperative. This means that to remain a study participant, the patient may not learn which of the two groups they were randomized to until one year postoperative. However, should the patient be unsatisfied with their outcome prior to that mark, they may elect to withdraw themselves from the study and learn which treatment they received and pursue further treatment if appropriate.

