#### Sample size calculation

The primary outcome is the modified Mayo Elbow Performance score. A minimum clinically importance difference of 15 points has been derived for patients with rheumatoid arthritis [31]. In a study of patients with elbow dysfunction, standard deviations ranged from 17 to 19 points [28]. In order to attain a study power of 80 % to detect a minimally clinically important difference of 15 points on the MEPS primary outcome measure at one year follow-up using ANOVA to compare ATER versus sham, and assuming a standard deviation of 19 points as well as an alpha level of 0.05, a total sample size of 52 patients will be required (group sizes of 26) [31, 32]. However, adjusting for the remote possibility of 5 % of patients requiring un-blinding in the case of sham surgery (drop out), and a possible 15 % loss to follow-up yields a total sample size of 68 (34 in each group).

Assuming a recruitment and consent rate of 70 %, we would need to approach 97 patients to achieve our required sample size. Hospital records indicate that our clinic sees approximately 10 eligible patients per month, meaning we can feasibly achieve our required sample size within 10 months of enrollment.

Patients who are excluded from the trial intra-operatively and patients whose symptoms resolve prior to intra-operative randomization will only be followed clinically and not as part of this study.

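### The primary MEPS time point is given as both 1 year and 24 months, and only the 1-year assessment comes before patients may learn their allocation and cross over

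*Protocol article*

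**What the plan says.** One year is primary in three places in the protocol article:

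- Abstract, Methods: "The primary outcome will be the Mayo Elbow Performance Score (MEPS) at 1 year follow-up".
- Table 1, under Purpose and hypothesis: the column "T = 1 year^b^Postoperative" carries the footnote "b^Primary endpoint".
- Sample size calculation: the trial is sized "to detect a minimally clinically important difference of 15 points on the MEPS primary outcome measure at one year follow-up".

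Twenty-four months is primary in three others:

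- Purpose and hypothesis: the aim is superiority in "chronic lateral epicondylitis of the elbow at 24 months postoperative as measured by the Mayo Elbow Performance Score (MEPS"), and the hypothesis that follows names the same time.
- Primary outcome, MEPS: "Our primary outcome measure is elbow pain and function as measured by the MEPS at 24 months post-operative".
- Primary analysis: the comparison is made "between the two surgical treatment groups on an intention-to-treat basis at 24 months post-surgery as compared to baseline values".

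The section on contamination and co-intervention states: "There will be a possibility of cross-over after one year postoperative". It also says that participants who stay in the study do not learn their allocation until one year. A dissatisfied patient may withdraw before then, learn the allocation and pursue further treatment.

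**The concern.** The Purpose and hypothesis section disagrees with its own table, and the analysis section disagrees with the sample size section. A reader cannot tell which result decides the trial.

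The protocol's own rules make the two time points different. One year is the last scheduled MEPS before patients may be told their arm. The 24-month MEPS is taken up to 12 months after that. By then some sham patients may have had further treatment, and patients who know their allocation may be scoring an instrument that the Primary outcome section says can be completed entirely by the patient. Cross-over would tend to shrink the difference, while knowledge of allocation could widen it, so the net direction of bias is unknown. The trial chose a sham control in large part to protect patient-reported scores (Discussion), and that protection is assured only up to one year.

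Two statistical consequences follow. The power statement refers to one year and includes nothing for cross-over between 12 and 24 months. With two candidate primary time points on record, the choice could also be made after both results are known.

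**Working it through.** **Inputs.** From Sample size calculation: difference 15 points, SD 19, alpha 0.05, power 80%, 26 per group (52 in total), 5% un-blinding counted as drop-out, 15% loss to follow-up, 68 enrolled. From Randomization: 1:1 allocation. From Primary analysis: ANCOVA with baseline MEPS. Assumed here, because the document gives no figure: the cross-over share *c*, full benefit in those who cross over, SD unchanged by cross-over, a baseline correlation of 0.5, and the correlation between the 12- and 24-month test statistics.

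**1. The plan's own figure.** Per-arm n = 2(1.960 + 0.842)² × 19² / 15² = 25.2, rounded up to 26, or 52 in total. This matches the plan with a two-sided alpha; a one-sided alpha would give 20 per arm. Exact power at 26 per arm (noncentral t, 50 df, noncentrality 15 / (19√(2/26)) = 2.85) is 79.7%. For attrition, 26 / 0.80 = 32.5, so 33 per arm and 66 in total. The exact-t size of 27 per arm gives 27 / 0.80 = 33.75, so 34 per arm and 68. The plan's 68 is therefore consistent.

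**2. What the figure covers.** The 5% allowance is for un-blinding treated as drop-out. Nothing is added for patients who stay in the trial and cross over after one year.

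**3. Dilution at 24 months, as illustration.** The intention-to-treat difference becomes 15(1 − *c*). The ANCOVA column uses a residual SD of 19√(1 − 0.5²) = 16.5. Power is two-sided at 0.05 with 26 per arm.

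| Assumed sham cross-over | Difference (points) | Power, unadjusted | Power, ANCOVA, correlation 0.5 |
|---|---|---|---|
| 0% | 15 | 80% | 90% |
| 20% | 12 | 61% | 73% |
| 40% | 9 | 39% | 49% |

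If all 34 per arm were analysed without adjustment, power would be 73% at 20% cross-over and 49% at 40%.

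**4. Picking the time point afterwards.** With two correlated standard normal statistics and no true effect, type I error is 1 − P(|Z₁| ≤ 1.96 and |Z₂| ≤ 1.96). At assumed correlations of 0.5, 0.7 and 0.8 this is 9.1%, 8.3% and 7.8%, against the nominal 5%.

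**The case against.** - **Contamination.** A reader might infer that the 24-month comparison is contaminated. The document says only that cross-over is possible. It gives no rate and does not say which arm may cross over or to what treatment, so sham patients receiving a late release is a reasonable inference and not protocol text. The comparison is open to contamination of unknown size. Intention-to-treat at 24 months remains a valid treatment-policy comparison, though a possibly diluted and partly unblinded one that does not isolate release from sham.
- **Sample size.** A reader might infer that it is wrong, or that the 80% cannot apply at 24 months. The arithmetic is right. The 15 points and SD 19 come from other elbow populations and are not described as specific to one year. The same 52 would serve 24 months if those values held and nobody crossed over.
- **Size of the power loss.** The unadjusted figures are pessimistic, since the plan uses ANCOVA. Full benefit in crossers is also an upper case, because they would have had less than 12 months to recover. Power still falls, so this affects the size and not the direction.
- **Two primary tests.** The document does not plan to test both time points as primary. The 8% to 9% applies only if the choice follows the results.
- **Blinded assessor.** Follow-up examinations use one, which protects the examination but not the answers of a patient who knows the allocation.
- **One year is not spotless.** Dissatisfied patients may withdraw and learn their allocation earlier, which could leave outcome-related gaps at 12 months. That stands, and naming 12 months does not cure it.
- **Natural history.** A reader might argue that the stated course of 6 to 24 months makes 24 months uninformative. With at least 6 months of symptoms at entry, patients are already at least 6 + 12 = 18 months from onset at the 1-year visit, so the argument bears on both time points and is not relied on here.

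**Conclusion.** The contradiction is plain on the face of the document and needs correction before analysis. It is not a product of condensing a longer protocol: the article states both versions, and an analysis plan that chose one would still conflict with half of it. The two time points cannot be swapped, because permitted disclosure and possible cross-over begin between them.

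The size of the effect at 24 months cannot be known from the document. The table in the working shows what assumed cross-over of 20% or 40% would do, and the type I error figures rest on assumed correlations. With no cross-over and the same difference and SD, the power at 24 months would be as stated.

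**What to change.** Name MEPS at 12 months as the single primary endpoint in Purpose and hypothesis, Primary outcome and Primary analysis, so that they agree with the abstract, Table 1 and Sample size calculation. State that the 12-month MEPS is completed before any disclosure of allocation. Make 24 months a secondary comparison, labelled as open to unblinding and cross-over.

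If the sponsor prefers to keep 24 months as primary, it should change the abstract, Table 1 and the sample size text instead, define the estimand and the handling of data after cross-over, and restate the power under a stated cross-over rate. For scale, using the unadjusted formula, 80% power would need 25.19 / (1 − *c*)² per arm. That is 40 per arm (80 evaluable, 80 / 0.80 = 100 enrolled) at 20% cross-over, and 70 per arm (140 evaluable, 140 / 0.80 = 175 enrolled) at 40%.

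The first option costs a wording amendment and a check that the registry entry, not seen here, agrees. The 12-month MEPS is already scheduled and 68 enrolled stands, so no patients, visits or procedures are added. Patients' access to unblinding or further treatment does not change. The downside is that the 24-month result becomes supportive only.

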### Randomization

The patients will be brought to the operating room where they will undergo a regional block anesthetic. A diagnostic arthroscopic evaluation will then be performed through a medial portal. Following this, the surgeon will make a decision as to whether the elbow requires any debridement. The decision to debride is a clinical one and is influenced by the presence of an intra-articular pathology, such as extensive synovitis (inflammation), loose bodies and radiocapitellar plicae. Patients who are deemed to require intra-articular debridement will receive it at this point. This requires the creation of a lateral, working portal. Patients who do not require debridement will be randomized to ATER or sham. Similarly, patients who do require debridement will be randomized to ATER or sham.

A randomization sequence will be computer generated by an independent statistician. Consecutive patients will be randomized to receive ATER or Sham surgery in a 1:1 allocation ratio, with stratification by the need for debridement and randomly permuted block sizes from 2, 4, or 6. Central randomization will be accomplished by the use of online registration and verification of eligibility through the Data Management Services group at the Ottawa Hospital Research Institute Fig. 1.

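### The primary test uses a fixed ANCOVA, but the effect estimate comes from a second regression whose extra covariates are picked by observed baseline imbalance

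*Protocol article*

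**What the plan says.** The Primary analysis section describes two models for one comparison.

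- **Test.** "A two-sample independent ANCOVA will be used to assess whether there is a statistically significant difference between groups for the MEPS scores", with the model "accounting for the debridement stratification variable and baseline MEPS".
- **Estimate.** "Linear regression will be used to estimate treatment size effect", and this model is "accounting for the stratification variable and baseline MEPS, as well as any possible imbalanced covariates".

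The first covariate set is closed. The second contains the first plus an open set whose membership is decided by imbalance. Nothing else in the article narrows that set. Table 1 lists 11 patient characteristics recorded at baseline (age, sex, symptom duration, affected arm, dominant arm, height, weight, BMI, occupation, smoking, diabetes), and none is singled out for adjustment.

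The Randomization section states: "Consecutive patients will be randomized to receive ATER or Sham surgery in a 1:1 allocation ratio, with stratification by the need for debridement". Apart from the stratification factor, then, any baseline difference between the arms arises by chance.

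**The concern.** An ANCOVA with treatment, stratum and baseline MEPS is itself a linear regression. Its treatment coefficient is the adjusted mean difference and comes with a confidence interval. A second regression is not needed to obtain an effect size. By adding it with a different covariate set, the plan separates the estimate from the test.

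The selection criterion is also a poor one. In a randomised trial, adjustment is worthwhile for covariates that predict the outcome. Observed imbalance is chance, can be judged only once the allocated patients' baseline data exist, and says nothing about prognostic value. An analysis plan that named covariates in advance would replace this criterion rather than fill it in, so the point is more than missing detail.

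What is at stake is the size of the effect that readers take away and the interval around it. A significant test could stand beside an interval that includes zero, or the reverse, and the estimate could vary with which variables are called imbalanced.

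**Working it through.** **1. The plan's own sample size.** The Sample size calculation section gives a difference of 15, SD 19, 80% power and alpha 0.05 (taken as two-sided). The normal approximation is n per group = 2 × (1.960 + 0.842)² × 19² / 15² = 2 × 7.85 × 361 / 225 = 25.2, rounded up to 26, or 52 in total as stated. Power at 26 per group is 0.812 (0.797 with the t distribution). Inflation gives 26/0.80 = 32.5 or 26/(0.95 × 0.85) = 32.2. Either rounds to 33 per group (66), within two patients of the stated 68. The sample size is not in dispute; it supplies N and SD for what follows.

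**2. One model gives agreement by construction.** In an ANCOVA with two arms the treatment F statistic has 1 numerator degree of freedom and equals t², where t = estimate / SE. Hence p < 0.05 exactly when the 95% interval excludes zero. With two covariate sets this identity is lost.

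**3. How often something looks imbalanced.** With k independent covariates screened at level a, P(at least one flagged) = 1 − (1 − a)^k.

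- k = 11: 1 − 0.95¹¹ = 43%; 1 − 0.90¹¹ = 69%.
- k = 10: 1 − 0.95¹⁰ = 40%; 1 − 0.90¹⁰ = 65%.

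A rule based on a standardised difference above 0.2 flags at least one in almost every simulated trial. Height, weight and BMI are linked, so independence overstates the first two figures somewhat.

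**4. Simulation of the two models.** There were 3,000 trials per setting. SD 19 and the N values come from the article. The other inputs are assumptions: 11 independent covariates jointly explaining 20% of variance, correlation 0.4 between baseline and follow-up MEPS, and a 28% debridement share (borrowed from the retrospective series in the Background). Percentages of trials in which the ANCOVA p-value and the regression interval disagree on significance:

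| N | True difference | p<0.05 screen | p<0.10 screen | Std. difference >0.2 |
|---|---|---|---|---|
| 52 | 10 | 6.3 | 10.6 | 20.9 |
| 52 | 15 | 4.9 | 7.4 | 12.0 |
| 68 | 10 | 7.1 | 10.3 | 17.8 |
| 68 | 15 | 2.6 | 4.0 | 6.5 |

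At a true difference of 0 and N = 52 the range is 2.5 to 5%. A simulation with 27 per arm, 10 covariates and a p<0.10 screen gave 6.6% at 15 and 11.2% at 10. Over all runs at 52 to 54 patients the range at 15 is about 4 to 12%.

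**5. How far the estimate moves.** The 95th percentile of the absolute gap between the two estimates is about 4 to 6.5 points at N = 52 and 3 to 5 at N = 68. The mean absolute gap is about 2 points among trials in which a covariate is selected, but only about 0.8 to 1.3 over all trials.

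**6. Bias and error rate.** When a rule is applied mechanically to baseline data, the regression's mean estimate at N = 52 is 15.0 to 15.3 for a true 15, and it rejects under the null in 3.7 to 4.4% of trials. If instead the single added covariate were picked for its effect on the result, the regression would reject in 9 to 10% of null trials, and at N = 52 the mean estimate would rise from 14.9 to 16.4 for a true 15.

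**The case against.** Several counter-arguments have force.

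- *The confirmatory decision is protected.* The open clause attaches only to the estimation model. This stands in full. A reader might infer that the trial's type I error is inflated; the text does not support that, because the test's covariates are fixed.
- *Imbalance is a property of baseline data.* A reader might also infer that covariates will be chosen in the light of outcomes. The article does not say so, and step 6 shows that a baseline-only rule does not bias the estimate on average. The 9 to 10% and 16.4 figures describe a misuse that the wording leaves possible, not one that it plans.
- *Lists and thresholds belong in an analysis plan that is not shown.* This is correct, and their absence is not the point here. The two covariate sets and the choice of imbalance as criterion are stated in the article itself.
- *The ANCOVA difference may be reported too, and the 15 points serve only to size the trial.* Both are possible. But the article assigns estimation of the effect to the regression, and readers will naturally set that estimate beside the 15-point difference.
- *Two valid models near the 5% boundary will sometimes disagree.* This is true, and it would also hold for a primary and a sensitivity analysis. The difference is that a labelled sensitivity analysis leaves no doubt about which result is primary.

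**Conclusion.** The point holds in a limited form. The primary analysis has a fixed model for the test and a data-dependent one for the estimate, and the latter selects on chance imbalance instead of prognostic value. The consequence is possible disagreement between p-value and interval, and room for discretion in the reported effect. It is not a threat to the validity of the primary test, nor evidence of planned bias.

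In size, about 40 to 70% of trials would flag a covariate under a p<0.05 or p<0.10 screen. Test and interval would disagree in about 4 to 12% of trials at a true difference of 15 and 6 to 21% at 10, with 52 to 54 evaluable patients. At 68 patients the disagreement at 15 falls to roughly 3 to 7%. The reading of the text is certain. These figures are not: they depend on the number, independence and prognostic strength of the covariates and on the screening rule, none of which the article gives. The change is worth making mainly because it costs nothing.

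**What to change.** In the Primary analysis section:

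1. State that the primary p-value, adjusted mean difference and 95% confidence interval all come from one ANCOVA with treatment, debridement stratum and baseline MEPS.
2. Delete the words on imbalanced covariates from the regression sentence; the separate regression then becomes redundant.
3. If further adjustment is wanted, name one or two prognostic covariates (symptom duration is a candidate in Table 1) before unblinding, and report that model as a labelled sensitivity analysis.

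Disagreement between the primary test and its interval is then 0% by construction. The cost is an edit to one paragraph, with no change to sample size, data collection or randomisation.

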Surgical indications for the management of lateral epicondylitis include persistent pain and failed adequate conservative management. The goals of surgery are to directly address that area of pathology through a procedure that involves resection of the involved tissue, to stimulate neovascularization and to produce a healthy scar while doing the least possible damage to surrounding tissues [16]. Current surgical options can be classified into open, percutaneous and arthroscopic, with arthroscopic tennis elbow release (ATER) having gained popularity over the past fifteen years with improved understanding of three-dimensional elbow anatomy and advances in arthroscopic procedures and equipment. When performed by experienced specialists, arthroscopic surgery allows for the assessment and debridement of concomitant intra-articular pathology such as synovitis, radiocapitellar plicae, osteochondral defects and intra-articular loose bodies that are often missed and can be a frequent cause of residual pain following extensor carpi radialis brevis (ECRB) release [17–20]. For example, in a retrospective review of 36 patients treated arthroscopically for tennis elbow, 28 % had significant intra-articular synovitis requiring debridement [21]. The rehabilitation process and time back to work following arthroscopic treatment is faster in comparison to the other surgical approaches and the outcomes are generally reported as equal or better [17, 19, 22, 23]. A recent retrospective cohort study on 341 consecutive patients comparing arthroscopic to open release demonstrated significant differences in Disability of the Shoulder and Hand (DASH) scores and total number of excellent outcomes between groups, favoring arthroscopy [24].

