#### Secondary analysis

A generalized estimated equations (GEE) analysis will be conducted to determine whether there is an effect of treatment arm over time (repeated measures) on the MEPS outcome, considering measures taken preoperatively, and at 3, 6, 12 and 24 month follow-ups. Other secondary analyses involves a comparison of the secondary outcome measures between the two surgical treatment groups. Differences in the mean abbreviated DASH and ASES-e scores, as well as grip strength, will be tested with ANOVAs and effect sizes estimated with linear regression. Median time back to work in each group will be derived with Kaplan-Meier survival curves, and a statistical comparison between groups will be tested using a log rank test.

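### The protocol aims to find out whether the ATER effect differs by need for debridement, but it only repeats the primary analysis in each subgroup and names no direct comparison of the two effects

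*Protocol article*

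**What the plan says.** Under Purpose and hypothesis, the protocol article lists, after the main comparison, the aim to "determine if there is a differential effect of ATER versus sham surgery among the subgroup of patients requiring additional elbow debridement". Randomization is stratified on the same factor (Study design; Randomization).

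The Primary analysis section uses debridement in two ways:

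- The overall ANCOVA and regression are fitted "accounting for the debridement stratification variable and baseline MEPS". This enters debridement as an adjustment covariate.
- It then says: "Primary analyses will be repeated for the debridement and no-debridement patient subgroups".

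The Secondary analysis section adds a GEE to "determine whether there is an effect of treatment arm over time (repeated measures) on the MEPS outcome". No debridement term is mentioned there. The Sample size calculation covers only the overall comparison of ATER with sham.

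**The concern.** Whether an effect differs between two groups of patients is a question about the difference between two treatment effects. Repeating the primary analysis in each stratum asks, twice, whether an effect differs from zero. The two verdicts can disagree because the strata differ in size, or by chance, while the effects are the same.

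Debridement is the stratification factor and the only subgroup question the article names. With no comparison specified, a result that is significant in one stratum and not in the other is the pattern most easily written up as a differential effect. The useful question is how often that pattern would arise when no difference exists.

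**Working it through.** **Inputs.** From Sample size calculation: a target to "detect a minimally clinically important difference of 15 points on the MEPS primary outcome measure", "assuming a standard deviation of 19 points as well as an alpha level of 0.05", 80% power, 52 evaluable patients (26 per arm), 68 after inflation. The same section reports that in the cited study "standard deviations ranged from 17 to 19 points", so both ends are tried. From Randomization: 1:1 allocation within debridement strata.

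**Assumption.** The article does not give the expected debridement share for this trial. The nearest figure, in Background, is a retrospective series of 36 in which 28% "had significant intra-articular synovitis requiring debridement". The trial's criteria also list loose bodies and plicae, so the share could be higher. The range used is 28% to 50%. By symmetry, 50% to 72% gives the same results.

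**Step 1: the plan's own figure.** n per arm = 2 × (1.960 + 0.842)² × 19² / 15² = 25.2, rounded up to 26, total 52. This reproduces the stated number with a two-sided test (power 79.7% by noncentral t).

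**Step 2: power within each stratum.** With m patients per arm in a stratum, SE = SD × √(2/m), and power follows from the noncentral t with 2m − 2 degrees of freedom. For 52 patients, a 28% share and SD 19:

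- Debridement: 26 × 0.28 ≈ 7 per arm, SE = 19 × √(2/7) = 10.2, power 27.5%.
- No debridement: 19 per arm, SE = 19 × √(2/19) = 6.2, power 65.8%.

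**Step 3: chance that exactly one stratum is significant.** With the same true 15-point effect in both, this is p₁(1 − p₂) + p₂(1 − p₁). Here 0.275 × 0.342 + 0.658 × 0.725 = 0.094 + 0.477 = 0.571.

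| Analysed | Share | SD | Per arm (debridement / none) | Power (debridement / none) | Exactly one significant |
|---|---|---|---|---|---|
| 52 | 28% | 19 | 7 / 19 | 27.5% / 65.8% | 57.1% |
| 52 | 28% | 17 | 7 / 19 | 33.0% / 75.4% | 58.6% |
| 52 | 50% | 19 | 13 / 13 | 48.9% / 48.9% | 50.0% |
| 52 | 50% | 17 | 13 / 13 | 57.9% / 57.9% | 48.8% |
| 68 | 28% | 19 | 10 / 24 | 38.7% / 76.3% | 56.0% |
| 68 | 28% | 17 | 10 / 24 | 46.3% / 84.9% | 52.6% |
| 68 | 50% | 19 | 17 / 17 | 60.7% / 60.7% | 47.7% |
| 68 | 50% | 17 | 17 / 17 | 70.4% / 70.4% | 41.7% |

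The range is 42% to 59%. Baseline adjustment does not remove the problem: with an assumed baseline correlation of 0.3 to 0.5, 52 patients and SD 19 (residual SD = 19 × √(1 − ρ²)), the figure is 48% to 59%.

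**Step 4: no effect in either stratum.** 2 × 0.05 × 0.95 = 9.5%.

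**Step 5: direct comparison.** The interaction is the difference between the two stratum effects, with SE = SD × √(2/m₁ + 2/m₂) and N − 4 degrees of freedom. For 52 patients and SD 19:

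- 28% share: SE = 19 × √(2/7 + 2/19) = 11.9. The 95% half-width is 2.01 × 11.9 = 23.9 points.
- 50% share: SE = 19 × √(4/13) = 10.5. The half-width is 21.2 points.

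In 40,000 simulated trials per split with equal 15-point effects, this test was falsely positive in 5.0% and 5.1%. Its power for a true 15-point interaction is 24% (28% share) to 29% (50% share). Power of 80% would need about 250 or 202 evaluable patients respectively.

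**The case against.** **No reading rule is stated.** The article nowhere says that one significant and one non-significant subgroup will be taken as a differential effect, and its hypotheses include none about subgroups. This stands. The percentages describe how often the misleading pattern would occur, not what the investigators have said they will conclude.

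**The comparison is not ruled out.** A reader might infer that the plan makes it impossible to test a difference. The documents do not support that. The primary analysis includes a regression that estimates the effect size, so repeating it yields an estimate in each stratum. The strata hold different patients, so the two estimates could be subtracted. What is lacking is any statement that this will be done.

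**The aim could be read more narrowly,** as ATER versus sham within the debridement subgroup alone. The word for a differing effect, and the rerun in both subgroups, fit the comparison better. Even on the narrow reading, power in that subgroup is only about 27% to 49% with 52 patients and SD 19, so a non-significant result would say little.

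**The analysis plan may supply the term.** This is a condensed article, and an interaction term would contradict nothing in it. But the article states both the aim and the analysis meant to serve it, and the two do not match. That is more than an omitted detail.

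**An interaction estimate will not settle the aim.** True, given its width. The gain is that the uncertainty is shown, where two separate verdicts would hide it.

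**Conclusion.** The point holds: the stated analysis does not answer the stated aim. If ATER has the same 15-point effect in both strata, the planned repetition gives discordant verdicts in about 42% to 59% of trials, against a 5% false-positive rate for a direct interaction test. This rests on a debridement share of 28% to 50%, an SD of 17 to 19, and 52 to 68 patients analysed. The upper number is generous: multiple imputation brings everyone into the analysis but does not restore the lost information.

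Three stronger readings are not supported:

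- That false differences would be frequent whatever the truth. The high figure needs a real, equal effect; with no effect it is about 9.5%.
- That the debridement subgroup is bound to be very small. This depends on a share near the 28% from one cited series, and the trial's own share is not stated. The conclusion survives an even split.
- That the wrong patients would be offered release. Need for debridement is decided during arthroscopy, so the step from a subgroup claim to patient selection is speculative.

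This is a secondary aim. The overall ATER versus sham test and its sample size are untouched.

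**What to change.** Replace the sentence on repeating the primary analyses with the following:

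- Fit one ANCOVA on all randomised patients with treatment, debridement, baseline MEPS and the treatment-by-debridement interaction.
- Report the interaction estimate with its 95% confidence interval as the answer to the differential-effect aim.
- Give the effect in each stratum with its confidence interval from the same model, without separate significance claims.
- Label the analysis exploratory, and state that the trial was not sized for it.

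The cost is a few lines of analysis text, with no extra patients, visits or data. The downside is that the subgroup conclusion becomes more modest, because the interval will often be too wide to confirm or exclude a difference as large as the 15-point target.
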